## 9.2 Dose and Dosage Regimen

Dose of each treatment group will be as follows:

Anticipated therapeutic dose: TS-071 5 mg

Supratherapeutic dose: TS-071 20 mg

Placebo: TS-071 placebo

Avelox: moxifloxacin 400 mg

Subjects will receive a single oral dose of a study drug assigned in each study period with 200 mL of water in the fasted state in the morning of study drug administration day according to the randomization code. There will be a wash-out interval of  $\geq 7$  days between each study period, i.e., when the preceding dose is on Day 1, the subsequent dose will be on Day 8 or thereafter.

<Rationale for the doses>

The doses for each treatment group, i.e., anticipated therapeutic dose, supratherapeutic dose, placebo and Avelox were determined based on the following results and assumptions:

- Anticipated therapeutic dose (TS-071 5 mg):

In the Phase II exploratory and confirmatory studies, statistically significant decreases in the change in HbA1c, which is the primary efficacy endpoint, and in the change in fasting blood glucose, which was

the secondary endpoint, were observed in all TS-071 dose levels (0.5 to 10 mg) compared to the placebo, whereas the extent of decreases was similar in the dose levels of  $\geq 2.5$  mg. Of the secondary endpoints tested, the changes in 2-hr postprandial blood glucose were larger in the groups receiving  $\geq 5$  mg compared to 2.5 mg in the Phase II exploratory study, and those in body weight were larger in the groups receiving  $\geq 5$  mg compared to 2.5 mg in the Phase II confirmatory study. With respect to safety, TS-071 was demonstrated to be well tolerated up to the dose of 10 mg.

The anticipated therapeutic dose is considered to be 2.5 mg, and the dose will be increased to 5 mg if sufficient effects are not demonstrated. The anticipated therapeutic dose for this study was thus determined to be 5 mg, which is the highest therapeutic dose of TS-071.

- Supratherapeutic dose (TS-071 20 mg):

The observed Cmax of unchanged TS-071 (299 ng/mL on Day 7) following 7-day repeated administration of TS-071 5 mg in the clinical pharmacology study (patient PK/PD) in patients with type 2 diabetes is regarded as the maximum exposure anticipated in the therapeutic use. The dose of 20 mg, which is expected to show substantially larger exposure, was selected as the supratherapeutic dose according to the QT/QTc Guideline. Based on the Phase 1 single dose study in Japanese healthy male subjects, the TS-071 dose range of 1 to 25 mg will pose no particular tolerability problem.

- Avelox:

In the thorough QT/QTc studies conducted in foreign countries Avelox 400 mg was generally employed as a positive control, which is also the approved daily dose in Japan.

#### <Rationale for the dosage regimen>

The amount of water to be taken with the study drug was determined according to “Guideline for Bioequivalence Studies of Generic Products”.

The interval between treatments of  $\geq 7$  days was selected to have an interval  $\geq 5$  times of  $T_{1/2}$  (see “9.1.3 Study Procedure and Period”) in reference to “Guideline for Bioequivalence Studies of Generic Products” and also considering the feasibility of the study.

### 9.3 Number of Subjects to be Enrolled

Fifty-six (56)

The number of male and female subjects in each treatment sequence should be as equal as possible. There will be 2 or more reserve subjects per admission group to stand by for study drug administration in Period 1, who will replace any withdrawn subjects prior to administration.

#### <Rationale>

The sample size was selected in reference to thorough QT/QTc studies carried overseas with a crossover design similarly to the present study since the results of thorough QT/QTc studies in Japanese subjects have not been made public to date.

## 9.4 Study Period

From June 13, 2011 to October 31, 2011

## 9.5 Evaluation Variables

### 9.5.1 Variables for QT/QTc Interval Analysis

The primary endpoint is QTcF, QT interval corrected by Fridericia's formula, and the secondary endpoint is QTcB, QT interval corrected by Bazett's formula.

#### <Rationale>

Fridericia's and Bazett's formulae will be used to correct QT interval according to the QT/QTc Guideline.

### 9.5.2 Safety Variables

- (1) Adverse events and adverse drug reactions, including abnormal changes in body temperature, blood pressure, pulse rate, 12-lead ECG and clinical laboratory tests
- (2) Effects on body temperature, blood pressure, pulse rate, 12-lead ECG and clinical laboratory tests

#### <Rationale>

These measurements were selected to investigate the effect on the subjects and confirm the safety of subjects.

### 9.5.3 Pharmacokinetic Variables

Plasma concentrations of unchanged TS-071 and its metabolites (M-2 and M-17), and plasma concentrations of unchanged moxifloxacin

#### <Rationale>

Plasma concentrations of unchanged TS-071 and unchanged moxifloxacin will be determined to investigate the relationship of their single-dose pharmacokinetics to QT/QTc interval in accordance with the QT/QTc Guideline, and also to confirm the pharmacokinetic parameters of TS-071 and moxifloxacin including Cmax, Tmax, AUC and T1/2.

## 10. Study Procedures

### 10.1 Demographics

The principal investigator or subinvestigator will capture the following subject's demographic information prior to study drug administration in Period 1 and document it in the CRF.

- (1) Date of birth
- (2) Ethnicity (Confirm that the subject is Japanese)
- (3) Gender
- (4) Present illness and its history that is ongoing at the time of study drug administration in Period 1
- (5) Medical history within the previous 5 years prior to informed consent; information on medical

history relevant to the exclusion criteria (2) to (4) before that period should also be captured.

- (6) Family history, i.e., present illness and its history and past medical history relevant to the risk factors for TdP
- (7) Drinking and smoking status
- (8) Height, weight and BMI at screening
- (9) Use of medications within one week prior to study drug administration in Period 1, including over-the-counter medications

## 10.2 Diet, Fluid and Activity Control and other Restrictions

Subjects will stay under supervision of the principal investigator or subinvestigator and will be instructed to adhere to the following instructions. The principal investigator or subinvestigator will check the adherence status at the time of physical examination.

Subjects will be discharged from the study site after the principal investigator or subinvestigator confirms that they have no abnormality in their healthy conditions as determined by the safety data up to 48 hr post-dose in each study period including physical examination, body temperature, blood pressure, pulse rate, 12-lead ECG and clinical laboratory tests.

When a prolongation of hospitalization, re-examination or additional examination is required for a subject at the discretion of the principal investigator or subinvestigator, he/she will prolong the hospitalization or perform unscheduled examination to confirm the subject's safety after explaining the reason and obtaining the subject's approval until there are no health concerns. Such unscheduled examinations or prolonged hospitalization will be documented in the CRF.

<Instructions to subjects and other study restrictions>

- (1) Subjects will rest in the supine position on the bed for 10 min (5 min at screening) prior to and during 12-lead ECG recording.
- (2) Beverages other than those provided at the study site will not be allowed during hospitalization. Consumption of any beverages will be prohibited within 2 hours before and 3 hours after study drug administration except water for dosing.

Consumption of caffeinated beverages and foods (e.g., coffee, red tea, oolong tea, green tea, cola, cocoa and chocolate), alcoholic beverages and those containing grapefruit will be prohibited within 2 days before admission to the study site through discharge in each study period and within 2 days before post-treatment examination through its completion. Excessive consumption of such beverages and foods will not be allowed including in the periods other than those described above.

- (3) Foods other than those provided at the study site will not be allowed during hospitalization. Consumption of any food will be prohibited within 10 hours before screening examination, examination on Day -1 and post-treatment examination.

Subjects will start fasting 10 hours before study drug administration and keep fasting until 4 hours after administration. Contents of meals during hospitalization (from supper on Day -1 through breakfast at 48 hr post-dose) will be consistent for the same subject and between subjects from Period 1 through Period 4, however, number of calories will be different for male and female subjects. Time of starting meals (supper on Day -1, lunch on Day 1, breakfast at 24 hr post-dose

and breakfast at 48 hr post-dose in each period) will be documented in the CRF.

- (4) Smoking will be prohibited after the time of informed consent through completion of post-treatment examination.
- (5) Strenuous physical exercise will be prohibited within 2 days before admission to the study site through discharge in each study period and within 2 days before post-treatment examination through its completion.
- (6) Use of medications other than the study drug including over-the-counter medications will not be allowed within one week before study drug administration in Period 1 through completion of post-treatment examination, except lacrimal fluid (eye lotion) for contact lenses. Medications may be used at the discretion of the principal investigator or subinvestigator when they are needed to secure the safety of the subject, e.g., to treat an adverse event. Use of other medications will be documented in the CRF according to “11.2.3 Adverse Event Assessments (6) Medical treatment for adverse event” when they are used to treat an adverse event; when they are used for the purpose other than an adverse event, name of medication, dosage regimen, period of administration (start and end dates) and purpose of use will be documented in the CRF.
- (7) Subjects will be instructed to use an adequate contraception after giving informed consent through completion of post-treatment examination.
- (8) Blood collection or donation for the purpose other than this study will be prohibited after giving informed consent through completion of post-treatment examination.
- (9) Urine glucose test (qualitative or quantitative) will not be allowed after study drug administration in Period 1 through 3 days after the final administration.

#### <Rationale>

- (1) This is intended to minimize the effect of excessive pulse change on 12-lead ECG.
- (2) Fluid consumption is likely to affect pharmacokinetics. The duration to prohibit fluid intake was determined considering the Tmax values of TS-071 after single administration of 5 mg, 15 mg and 25 mg (1.06 hr, 1.56 hr and 2.25 hr, respectively) and that of Avelox® tablets after single administration (1.75 hr). Caffeine and alcohol are likely to impact on diuresis, hepatic and renal drug metabolism, QT/QTc interval and transaminase values. Grapefruit-containing foods and beverages are likely to affect pharmacokinetics.
- (3) These restrictions are intended to exclude the effect on variables for evaluation and also in reference to “Guideline for Bioequivalence Studies of Generic Products”.
- (4) Smoking is likely to affect gastrointestinal motility, drug absorption and QT/QTc interval.
- (5) Escape enzymes from musculoskeletal muscle caused by strenuous exercise, such as AST (GOT) and CK (CPK), are likely to confound the safety evaluation and affect QT/QTc interval.
- (6) Use of other medications may confound the protocol-directed evaluation. The principal investigator and subinvestigator will be allowed to prescribe concomitant medications at his/her own discretion to assure the safety of subjects.
- (7) Safety in pregnancy is not established for the treatment of either TS-071 or Avelox® tablets. In addition, effects of TS-071 exposure via semen on the safety cannot be excluded at present.

- (8) This is intended to assure the safety of subjects.
- (9) This is intended to maintain blinding of TS-071 treatments.

### 10.3 Confirmation of Study Drug Indistinguishability, Randomization and Dispensing Drugs

Confirmation of study drug indistinguishability, randomization and dispensing drugs will follow the procedures below. Further details will be shown in a written procedure to be prepared by the random assignment manager.

#### 10.3.1 Confirmation of Study Drug Indistinguishability

The random assignment manager will verify that the study drugs (TS-071) are identical in appearance in terms of their color, shape, size and smell prior to study drug administration of the first subject in Period 1 and at the time of retrieving study drugs to the sponsor to make sure that the blinding of study drugs is maintained. The random assignment manager will create 2 sets of documents verifying the maintenance of blinding after all the relevant procedures, retain one of the documents and provide the other to the sponsor.

#### 10.3.2 Randomization

##### 10.3.2.1 Assigning Treatment Sequences

The random assignment manager will randomly assign treatment groups to determine the order of treatments within each treatment sequence by the time of study drug administration to the first admission group in Period 1 according to the predetermined procedure. A randomization code will be created for each treatment sequence, sealed and securely retained until unblinding. The randomization codes of treatment sequences will be provided to the sponsor after unblinding. Prior to sealing the randomization codes, the random assignment manager will create randomization codes of study treatments for each admission group, and then seal the randomization codes of treatment sequences according to the procedure described in “10.3.2.2 Assigning Study Treatments.”

##### 10.3.2.2 Assigning Study Treatments

The random allocation manager will randomly assign study treatments according to the predetermined procedure. The random allocation manager will create randomization codes of study treatments that list subject identification codes and corresponding treatment sequences according to the randomization codes of treatment sequences, and seal the original codes and their duplicates separately. The randomization codes of study treatments may be unblinded by the random allocation manager according to the procedure described in “10.3.3 Dispensing Study Drugs.” The randomization codes of study treatments will be securely retained by the random allocation manager and their duplicates will be provided to the drug assay laboratories.

#### 10.3.3 Dispensing Study Drugs

The random assignment manager will dispense the study drugs and document the dispensing according to the “Procedure for study drug management.”

The study drugs will be dispensed for each admission group prior to study drug administration in each study period. The randomization codes of study treatments will be unblinded every time the study drugs are

dispensed and sealed again after dispensing.

#### 10.3.4 Assigning Study Treatments to Subjects

On Day 1 of Period 1, the principal investigator will allocate a subject identification code to each subject who is to receive study drug administration (see “7.2 Subject Registration List”) and administer the dispensed study drug to each subject. When a subject who is to receive study drug administration is replaced by a reserve subject, the replacing subject will receive the study drug that is planned to be administered before replacement.

### 10.4 Blinding Procedure and Maintenance of Blinding

The procedures for blinding and maintaining blinding are described below. Further details will be shown in a written procedure to be prepared by the random assignment manager.

#### 10.4.1 Treatments to be Blinded

Treatments of anticipated therapeutic dose, supratherapeutic dose and placebo will be double-blinded, and treatment of Avelox will not be blinded. 12-lead ECG data for QT/QTc analysis for all the treatments will be read by the blinded ECG readers at the central ECG analysis facility.

#### 10.4.2 Blinding of Study Treatments and Maintenance of Blinding

The random allocation manager will securely retain the randomization codes of study treatments until unblinding, and should not disclose the allocated treatments to any party until unblinding, except when unblinding emergency keys.

The responsible person at the drug assay laboratories will securely retain the duplicates of the randomization codes of study treatments and unblind them prior to drug assay. The responsible person should not disclose the allocated treatments to any third party including the sponsor, central ECG analysis facility, study site and the drug assay consigner prior to unblinding.

The treatment of Avelox will not be blinded, however, the ECG readers at the central ECG analysis facility will be blinded to all the treatments. Appropriate measures should be taken to maintain the blinding of ECG data, e.g., shielding the time of recording 12-lead ECG charts and subject identification information in accordance with the procedure of the facility.

#### 10.4.3 Blinding of Urine Glucose Test

Urine glucose (qualitative or quantitative) should not be tested to maintain blinding after study drug administration in Period 1 through 3 days after the final administration.

#### 10.4.4 Creating and Retaining Emergency Keys

The random allocation manager will create 2 sets (original and duplicate) of emergency keys and seal them separately. The original keys will be retained by the sponsor and the duplicates by the random allocation manager. The emergency keys will only be unblinded in accordance with the predetermined procedure (see “10.4.5.2 Unblinding Emergency Keys” for unblinding.)

Emergency keys will be created and sealed separately for each subject in each study period so that the study treatment of a relevant subject in a relevant study period can be unblinded.

Prior to the unblinding procedures, the random allocation manager will verify that the original and duplicate emergency keys are sealed and provide both original and duplicate keys to the sponsor after unblinding. When an emergency key has been unblinded, the random assignment manager will verify that the emergency keys other than those unblinded are sealed.

#### 10.4.5 Unblinding Procedures

##### 10.4.5.1 Unblinding Randomization Codes

The random allocation manager will unblind the randomization codes of treatment sequences and those of study treatments after all the CRF data are entered, safety and QT/QTc analysis data including their handling are fixed, and the randomization codes are confirmed to be sealed. After unblinding, the randomization codes of treatment sequences and those of study treatments will be provided to the sponsor.

##### 10.4.5.2 Unblinding Emergency Keys

When a serious adverse event occurs and the principal investigator or subinvestigator finds it necessary to unblind the subject's emergency key to secure the safety, he/she will contact the sponsor to unblind the subject's emergency key of the relevant study period and document in the CRF the information including the subject identification code, relevant study period, reason for unblinding and safety data. When the sponsor finds it necessary to unblind the emergency key, the sponsor monitor will confirm that the above information is entered in the CRF, unblind the emergency key without delay, and inform the principal investigator or subinvestigator of the allocated treatment. The principal investigator will record the unblinding procedure of the emergency key upon consultation with the sponsor and provide the sponsor with the record. The sponsor will report the allocated treatment and the reason for unblinding to the medical expert and the random allocation manager. The handling of the relevant subject's data will be determined by the sponsor.

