## 11. Securing the Safety of Subjects

### 11.1 Basic Principles

- (1) The principal investigator will be responsible for all medical decisions involved in the conduct of the study.
- (2) The head of the study site and the principal investigator will assure that all subjects will be provided with adequate medical care for every adverse event that may occur in relation to this study during and after their participation in the study.
- (3) The sponsor will be responsible for evaluating the safety of study drugs continuously.
- (4) The sponsor will promptly provide the principal investigator and the head of the study site with any information that may affect the safety of subjects, the conduct of the study, or the approval of the IRB for continuation of the study.

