### 16.3 Guidance for Completion of CRFs

- (1) CRFs will be entered by using a writing tool such as indelible black ballpoint pen.
- (2) Amendments or deletions of entries or additional entries after the date of preparation will be made by crossing out with a double line so that the original entries remain legible, and by a signature or seal/sign with the date. Changes in important data should be accompanied by an explanation. Important data will include the subject identification code, entries relating to informed consent, assessment of eligibility (except comments), normal/abnormal assessment of 12-lead ECG, normal/abnormal assessment of urine sediment, abnormal change in examinations (body temperature, blood pressure, pulse rate, 12-lead ECG and clinical laboratory tests), entries relating to adverse events (presence/absence of adverse event, adverse event term, severity, seriousness and relationship to study drug) and entries relating to early termination (except comments.)
- (3) The signatures/seals of the principal investigator, subinvestigator and clinical research coordinator to be used in the CRFs must be consistent with those presented in a separate "List of Signatures and Seal Impressions."
- (4) Except for blank spaces to be used for follow-up examination and documentation of medical history, concomitant medications and adverse events, all blank spaces will be crossed out with a diagonal stroke or explained to distinguish them from missing entries.
- (5) Strips of laboratory reports will be attached to the relevant pages of the CRF. The principal investigator, subinvestigator or clinical research coordinator will sign or affix a seal over the edges of the two documents.

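### After the investigator has judged emergency unblinding necessary for safety, the key still opens only once the sponsor agrees and its monitor confirms the CRF entry

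*Protocol*

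**What the plan says.** Protocol 10.4.5.2 starts from this situation: "When a serious adverse event occurs and the principal investigator or subinvestigator finds it necessary to unblind the subject's emergency key to secure the safety". In that case "he/she will contact the sponsor to unblind the subject's emergency key of the relevant study period", and the investigator records the identification code, the period, the reason and the safety data in the CRF.

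The next sentence passes the matter to the sponsor: "When the sponsor finds it necessary to unblind the emergency key, the sponsor monitor will confirm that the above information is entered in the CRF". The same sentence then has the monitor "unblind the emergency key without delay, and inform the principal investigator or subinvestigator of the allocated treatment". Afterwards the sponsor tells the medical expert and the random allocation manager what was given and why the key was opened, and the sponsor decides how that subject's data are treated.

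On custody, 10.4.4 says: "The original keys will be retained by the sponsor and the duplicates by the random allocation manager". On exclusivity it says: "The emergency keys will only be unblinded in accordance with the predetermined procedure", with a cross-reference to 10.4.5.2. Separate keys are made for each subject in each period.

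Two other sections bear on this. Section 11.1(1) says: "The principal investigator will be responsible for all medical decisions involved in the conduct of the study". Section 16.3 shows that the CRF is handwritten: "CRFs will be entered by using a writing tool such as indelible black ballpoint pen". Under 10.4.1, the two TS-071 doses and placebo are double-blind and Avelox is open.

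**The concern.** The procedure begins after the investigator has already concluded that a subject's safety requires the code. Two further steps, both in the sponsor's hands, then stand before the opening: the sponsor's own finding of necessity, and the monitor's confirmation that the CRF has been filled in. The protocol does not say what happens if the sponsor disagrees or cannot be reached, and it sets no time limit for either step.

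Followed as written, the rule can delay or block the code in the one situation for which emergency keys exist. It also places the deciding judgement with a party other than the person whom 11.1(1) makes responsible for medical decisions.

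A smaller matter follows from the same paragraph. Section 10.4.5.1 requires data handling to be fixed before the randomization codes are opened. For a subject whose emergency key has been opened, the sponsor knows the allocation and then decides the handling of that subject's data, and nothing in the text separates the two roles.

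**Working it through.** No arithmetic applies to the main point. The check is to put the steps in order and then look for another route to the code.

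**Order of steps in 10.4.5.2**
1. A serious adverse event occurs and the investigator judges unblinding necessary for safety.
2. The investigator contacts the sponsor and makes the CRF entries.
3. The sponsor in turn finds unblinding necessary.
4. The sponsor monitor confirms that the CRF entries exist.
5. The monitor opens the key and tells the investigator.

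Steps 3 and 4 come between the investigator's judgement and the opening. The requirement to act promptly attaches to step 5 and does not shorten steps 3 and 4.

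**Other routes considered**
- *Key at the site (10.4.4).* None is provided. The sponsor holds one set and the random allocation manager the other.
- *The duplicate set (10.4.2, 10.4.4, 10.4.5.2).* Section 10.4.2 exempts emergency-key opening from the random allocation manager's duty not to disclose. However, 10.4.5.2 gives the investigator no way to trigger that disclosure; the manager appears there only as someone informed afterwards.
- *Immediate-hazard clause (14.1).* This excuses a deviation made without the sponsor's prior agreement, but it supplies no key and names no route to one.
- *Separate written procedure (10.4).* The section says that further details will be set out by the random assignment manager. That document is not available. It may add contact details, but it should not reverse an order, and an exclusivity rule, that the protocol itself fixes.

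**Scope**
- Three of the four treatments are blinded. With 56 subjects, that is 56 × 3 = 168 of 56 × 4 = 224 planned administrations.
- The 168 counts blinded doses. It is not a count of affected doses, because the route is used only after a serious adverse event in which the investigator wants the code. Section 1.3 reports no serious adverse event in either Phase I study in healthy subjects.

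**The case against.** Several points on the other side are sound and limit what can be claimed.

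- **11.1(1).** A reader might infer a direct contradiction. The section does not say that opening a code is a medical decision, and 11.1(3) gives the sponsor continuing responsibility for evaluating drug safety. The supportable term is tension.
- **Promptness after a check.** A reader might say that 10.4.5.2 contradicts itself by asking for speed after a paper check. It does not: the demand for speed applies once the conditions are met. The monitor must confirm that the entries exist, and the text does not require sight of the page, so a telephone call could suffice.
- **Clinical need.** It is tempting to cite hypoglycemia or torsade de pointes as cases where care would wait for the code. The measures in 11.4.3 and 11.4.5 do not depend on the allocation, and the known QT-prolonging comparator is open-label. The point rests on 10.4.5.2 itself, which recognises that the code may be needed for safety.
- **Length of delay.** A reader might estimate it and compare it with the mean Tmax values. The documents give no figure for the delay, so the comparison has no basis.
- **Data handling.** The text says that the sponsor decides. It does not say that the staff who open the key are those who decide. The central ECG readers remain blinded to all treatments, so the reading of the QTcF data is protected.
- **No access in practice.** The protocol names no independent route for the investigator. Whether the duplicates could be reached under the unseen written procedure cannot be settled from this document.

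What remains is the order of the steps, the custody of the keys and the exclusivity rule. None of the points above removes these.

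**Conclusion.** The point holds in limited form. As written, the investigator's safety judgement is not enough to open a key: the sponsor's agreement and the monitor's CRF confirmation come before it, and the investigator has no route of their own to either set. The sponsor can still relay the code, so the defect is the lack of independent access and not a total lack of access.

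It concerns the three double-blind treatments, and only after a serious adverse event for which the investigator wants the code. Use should therefore be rare. The delay is unstated and no estimate is offered. The conclusion assumes that the separate written procedure does not override the order set in 10.4.5.2. Because the change is small and bears on subject safety, it should be made.

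**What to change.** Amend 10.4.4 and 10.4.5.2 together:

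- State that the judgement of the principal investigator or subinvestigator is enough to open, or obtain at once, the duplicate key for that subject and period, and say how the site reaches it.
- Make notification of the sponsor, the CRF documentation and the monitor's check follow the opening, so that none of them is a precondition.
- State that the handling of that subject's data is decided by sponsor staff who have not been told the allocation.

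The random allocation manager's written procedure needs matching text. The cost is wording only, since the duplicate keys already exist. The downside is slightly less sponsor control over unnecessary unblinding; having a separate key for each subject and period, together with the documentation that follows, limits this.
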